## Abstract

**Background:**

Two unfortunate outcomes for patients treated surgically for rectal cancer are placement of a permanent colostomy and local tumor recurrence. Total mesorectal excision is a new technique for rectal cancer surgery that can lead to improved patient outcomes. We describe a cluster randomized controlled trial that is testing if the above patient outcomes can be improved through a knowledge translation strategy called the Quality Initiative in Rectal Cancer (QIRC) strategy. The strategy is designed to optimize the use of total mesorectal excision techniques.

**Methods and Design:**

Hospitals were randomized to the QIRC strategy (experimental group) versus normal practice environment (control group). Participating hospitals, and the respective surgeon group operating in them, are from Ontario, Canada and have an annual procedure volume for major rectal cancer resections of 15 or greater. Patients were eligible if they underwent major rectal surgery for a diagnosis of primary rectal cancer. The surgeon-directed QIRC interventions included a workshop, use of opinion leaders, operative demonstrations, a post-operative questionnaire, and, audit and feedback. For an operative demonstration participating surgeons invited a study team surgeon to assist them with a case of rectal cancer surgery. The intent was to demonstrate total mesorectal excision techniques. Control arm surgeons received no intervention. Sample size calculations were two-sided, considered the clustering of data at the hospital level, and were driven by requirements for the outcome local recurrence. To detect an improvement in local recurrence from 20% to 8% with confidence we required 16 hospitals and 672 patients – 8 hospitals and 336 patients in each arm. Outcomes data are collected via chart review for at least 30 months after surgery. Analyses will use an intention-to-treat principle and will consider the clustering of data. Data collection will be complete by the end of 2007.

**Discussion:**

Lower rates of permanent colostomy and local tumour recurrence in the intervention arm would suggest the QIRC strategy is efficacious. The strategy may act as a template for efforts to improve surgical quality in other areas and will contribute to knowledge on influencing surgeon practice.

**Trial registration:**

Current Controlled Trials ISRCTN78363167

## Background

Surgical resection of rectal cancer is the cornerstone of curative therapy. Typically during rectal cancer surgery the tumour and a contiguous segment of normal bowel are removed and the bowel tract reestablished. For surgically treated patients two unfortunate outcomes are permanent colostomy and local tumor recurrence. For various reasons the operating surgeon may deem it necessary to remove the rectum and anus rendering the patient dependent on a permanent colostomy. Local tumor recurrence is defined as tumour that recurs in the pelvis near the previous operative site [1-3]. It is especially feared since this outcome is usually inoperable and patients, as a result, can suffer a slow, painful death. This study is testing if these two important outcomes, rates of permanent colostomy and local tumour recurrence, can be improved at the hospital level using the surgeon-directed Quality Initiative in Rectal Cancer (QIRC) strategy.

Studies on rectal cancer surgery outcomes usually show that rates of permanent colostomy, local tumour recurrence, and even patient survival vary markedly at the surgeon, hospital, or region level. For example, among the regions of Ontario, Canada researchers showed that rates of permanent colostomy following rectal surgery varied from 31% to 41% [4]. A study examining local tumour recurrence among surgeons operating in five hospitals in Edmonton, Alberta showed that rates varied from 10% to 45% based on surgeon specialty training and procedure volume [5]. These Canadian results are similar to studies in Europe [6-8]. The presence of important outcome variations suggests variation in the quality of delivered surgery.

Total mesorectal excision is a refinement of traditional surgical techniques that stresses sharp dissection of the mesorectum – the lymph node-bearing portion of the rectum – with careful autonomic nerve preservation [9-11]. There are a growing number of single institution series describing improvements in outcomes with the introduction of total mesorectal excision- in particular local tumour recurrence rates as low as 5% and permanent colostomy rates of 10–15% [12-18]. Population based studies from Europe also detail positive changes when surgeons in large areas adopt total mesorectal excision principles [19,20].

Knowledge translation research has identified interventions that may encourage physician behaviour change such as continuing medical education (e.g., workshops), use of opinion leaders, and audit and feedback [21-28]. It is also suggested that multiple interventions are more effective than single interventions. As well, behaviour change may be enhanced by using quality improvement principles such as a participatory and supportive approach that focuses on the system, not individuals; breaking processes down into definable steps that are more readily targeted for improvement; and, decreasing variation in process steps resulting in improved overall quality [29-32]. The QIRC strategy integrated such knowledge translation interventions and quality improvement concepts in an attempt to ensure that hospitals (i.e., the surgeons in the respective hospital) delivered optimal total mesorectal excision-type surgery to patients.

The purpose of this paper is to describe the methodology of our cluster randomized controlled QIRC trial, which is testing if the surgeon-directed QIRC strategy can improve patient outcomes at the hospital (i.e., cluster) level. We used a cluster design to minimize the chances of contamination at the patient and surgeon level. We surmised that patient-level randomization would not work since surgeons exposed to new information or techniques, such as those promoted through the QIRC strategy, would accept or reject such information or techniques for all of their subsequent patients. We surmised that surgeon-level randomization would not work since surgeons in a given hospital often share operative experiences through discussion or direct observation, and thus new information or techniques would likely be shared among surgeons in a given hospital. Since surgeons in Ontario rarely perform rectal cancer surgery at more than one hospital, we were confident that hospital-level cluster randomization would minimize the chances of contamination between the two arms of the QIRC trial.

## Methods and Design

### Study design

This study is a cluster randomized controlled trial with hospitals being the clusters. Hospitals were randomized to the QIRC strategy (intervention group) versus normal practice environment (control group). The QIRC strategy is directed at surgeons in hospitals randomized to the intervention group using a 1:1 allocation ratio.

### Participants

#### Hospitals

To avoid targeting sites with minimal procedure volumes, we stated that participating hospitals in Ontario, and the respective surgeon group operating in them, must have an annual procedure volume for major rectal cancer resections of 15 or greater. We identified 33 such hospitals using administrative data for the period April 1, 2000 to March 31, 2001. Hospitals were then excluded if they had participated in the QIRC pilot study [33] (3 sites), if the majority of rectal surgery was performed using laparoscopic techniques (2 sites), or if surgeons at the site were involved in the QIRC trial as rectal surgery experts (4 sites). These two latter criteria were needed since a key intervention of the QIRC strategy was operative demonstrations delivered by rectal surgery experts using open versus laparoscopic techniques (See Interventions below). Nine hospitals were excluded leaving 24 potential sites. Hospitals were then eligible if 60% or more of surgeons at the respective site consented to participate and if the respective research ethics board approved the study. Sample size calculations indicated the need for 16 sites. For the first 18 hospitals approached, nearly every surgeon consented to participate and 16 hospital ethics boards approved the study protocol. (Figure 1)

**Figure 1 F1:**
[figure not shown]
QIRC trial schema.

#### Patients

Patients were eligible if they underwent major rectal cancer surgery (i.e., partial or complete segmental resection of rectum with or without an anastamosis) for a diagnosis of primary rectal cancer. Thus patients who received local excisions were not eligible. We defined a rectal versus colon cancer as a tumour located within 15 cm of the anal verge by rigid sigmoidoscopy, or, a tumour at or below the level of the sacral promontory as seen at the time of surgery. These anatomic landmarks ensured the inclusion of patients that would potentially benefit from total mesorectal excision -type surgery. Tumour stage was not used as an exclusion criterion since issues of permanent colostomy and local recurrence are relevant to all patients undergoing surgery.

### Intervention

The QIRC strategy is a set of interventions directed at surgeons working in a given hospital. The interventions include: a workshop, use of opinion leaders, operative demonstrations, a post-operative questionnaire, as well as audit and feedback.

#### Workshops

These were used to introduce to participating surgeons all aspects of the study and new information. For the latter, topics included rectal cancer surgery outcomes in Ontario and elsewhere, total mesorectal excision, and, knowledge translation and quality improvement. The intent of the workshop was to promote thought in three areas: 1) There is a need to improve population level rectal cancer surgery outcomes in most jurisdictions. 2) The QIRC strategy may help surgeons improve these outcomes. 3) The pursuit of surgical excellence is an active and continuous process.

#### Opinion leaders

At each workshop, participating surgeons selected an opinion leader for their hospital using a validated approach [34]. In summary, the selection was based on the opinion leader having three attributes including a high level of clinical expertise, a willingness to share knowledge, and being educationally influential. The opinion leader acted as a local resource person on issues pertinent to the study. For example, the opinion leader encouraged their colleagues to participate in operative demonstrations.

#### Operative demonstration

Participating surgeons invited a study team surgeon to assist them with a case of rectal cancer surgery. The main intent was to demonstrate total mesorectal excision techniques. Surgeons were encouraged to participate in a minimum of two operative demonstrations. The participating surgeon retained full control over all peri-operative and operative decision-making.

#### Operative questionnaire

This questionnaire was completed after each rectal cancer surgery. The questions were designed to prompt surgeons to re-examine key total mesorectal excision operative steps [see Additional file 1].

#### Audit and feedback

Data (e.g., rates of permanent colostomy) were provided to individual surgeons and in a group forum for overall hospital results. The intent of feedback was to encourage individual surgeons to constantly self-examine surgical decision-making.

### Control arm

Hospitals in the control group represented the normal environment where the onus is on the individual surgeon to obtain new knowledge or skills for any aspect of the care they provide. Efforts to improve the quality of rectal cancer care among control arm surgeons were not facilitated by the study team.

### Objectives

#### Primary objective

We wish to test the efficacy of the QIRC strategy to improve hospital rates of permanent colostomy and local tumour recurrence among patients surgically treated for rectal cancer. We hypothesize that hospitals exposed to the QIRC strategy (intervention) will have better outcomes – lower rates of permanent colostomy and local tumour recurrence – compared to hospitals in the normal practice environment (control).

#### Secondary objective

We wish to test if the QIRC strategy can lead to improved quality of life, and improved bladder, bowel, and sexual function among patients surgically treated for rectal cancer. We hypothesize that patients treated in hospitals exposed to the QIRC strategy (intervention) will have higher scores on quality of life measures, and bowel, bladder and sexual function questionnaires compared to patients treated in control arm hospitals.

### Outcome measures

#### Primary outcomes

Since the hospital is our unit of analysis it is imperative that consecutive patients be included to prevent surgeon selection bias (e.g., excluding patients with difficult tumours perceived as high-risk for negative outcomes). Three methods of patient accrual were used to ensure consecutive patient accrual for primary outcomes – regular (weekly) phone calls to surgeons' offices, review of operating room booking logs, and hospital health records queries. Patient consent was not obtained for primary outcomes since data were collected via retrospective chart review and involved no patient contact. Primary outcomes included:

#### Hospital rate of permanent colostomy

It is usually known at the time of rectal cancer surgery if a person has received a permanent colostomy. However, in cases where a patient receives a temporary stoma 18 months will be allowed for temporary stoma closure, after which time the patient will be designated as having a permanent colostomy. An anastomosis of the rectum must also be functioning for at least three months to be considered a non-permanent colostomy. This will prevent a positive outcome being marked for a patient who subsequently receives a colostomy for problems such as an anastomotic leak or severe incontinence.

#### Hospital rate of local recurrence

Local tumor recurrence is usually defined as tumour that recurs in the pelvis near the previous operative site [1-3]. Most, though not all, local recurrences manifest within two years of surgery. In this study local recurrence in the pelvis will be defined in three ways:

1. Definite recurrence – positive histology.

2. Probable recurrence – a postoperative mass in the area of previous pelvic surgery with any of the following patient signs (hydronephrosis, invasion of pelvic structures, or bleeding rectal mass) or symptoms (deteriorating sexual function, deteriorating bladder function, deteriorating bowel function, or persistent and worsening lower back, perineal or sciatic pain).

3. Possible recurrence – based strictly on a patient developing any of the symptoms mentioned above (deteriorating sexual function, deteriorating bladder function, deteriorating bowel function, or persistent and worsening lower back, perineal or sciatic pain).

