### Data gathering

Data are being collected for patients in the intervention and control groups in identical ways. Primary outcomes data are collected via chart review for at least 30 months, and thus follow-up will be greater for all but the final patients enrolled in the trial. This follow-up period will allow identification of local recurrence events, since local recurrence typically occurs within two years of surgery [1-3]. Hospital charts are reviewed within two weeks of surgery and every three months thereafter. Regional Cancer Centre charts are also reviewed to optimize the collection of data on potential patient treatments (e.g., radiation therapy) and outcomes (e.g., local recurrence). In Ontario, all radiation therapy is delivered at a small number of such Cancer Centres. Quality of life and bowel, bladder, and sexual function were measured at four times: baseline (pre-operatively or within 4 weeks of surgery) and at 6, 12 and 18 months post-surgery. Trained assessors obtained data for secondary outcomes during telephone interviews. All data will be handled with strict confidentiality, and study reports or presentations will maintain patient, surgeon, and hospital anonymity. Data collection will be complete by the end of 2007.

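### The three local-recurrence tiers leave out an unbiopsied pelvic mass with no listed sign or symptom, even one that enlarges on imaging or is treated as recurrence

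*Protocol article*

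**What the plan says.** In the Protocol article, under Hospital rate of local recurrence, the definition is a closed list: "In this study local recurrence in the pelvis will be defined in three ways".

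- *Definite*: "Definite recurrence – positive histology".
- *Probable*: "a postoperative mass in the area of previous pelvic surgery with any of the following patient signs", with the signs and the alternative route given as "hydronephrosis, invasion of pelvic structures, or bleeding rectal mass) or symptoms". The listed symptoms are worsening sexual, bladder or bowel function and persistent, worsening pain at three named sites.
- *Possible*: "based strictly on a patient developing any of the symptoms mentioned above". No mass is needed.

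Under Data gathering, "Primary outcomes data are collected via chart review for at least 30 months", and "Hospital charts are reviewed within two weeks of surgery and every three months thereafter". A second source is added: "Regional Cancer Centre charts are also reviewed to optimize the collection of data on potential patient treatments (e.g., radiation therapy) and outcomes (e.g., local recurrence".

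Under Sample size, local recurrence at 20% versus 8% sets the trial's size: 8 hospitals and 336 patients per arm.

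**The concern.** Take a patient whose follow-up imaging shows a pelvic mass at the operative site that grows between scans. It is not biopsied, has none of the three listed signs, and causes none of the listed symptoms. The chart records a diagnosis of local recurrence and treatment for it. No tier admits this patient.

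The ordering is also odd. Worsening bowel function with no mass at all has a place in the scheme, while a growing mass that clinicians treat as recurrence has none. Abstractors are sent to the Cancer Centre charts for treatment and recurrence data, yet neither a recorded diagnosis nor a recorded treatment is a criterion in any tier.

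At stake is the count of events for the primary outcome that determined the sample size. Events lost in this way reduce the observed rates and the power.

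**Working it through.** **1. The case against each tier.** Inputs: no histology, no hydronephrosis, no invasion, no bleeding mass, no listed symptom; the mass enlarges or is treated as recurrence.

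| Tier | Requirement | Met? |
|---|---|---|
| Definite | positive histology | no |
| Probable | mass and (listed sign or listed symptom) | no: mass present, second part absent |
| Possible | listed symptom | no |

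Growth, diagnosis and treatment appear in no row. Changing one input shows where the gap ends: add hydronephrosis or invasion seen on imaging, still with no symptom, and *probable* is met. The article does not say which tiers make up the primary event, but this patient is outside every choice.

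**2. The plan's own sample size.** Inputs from Sample size: p1 = 0.20, p2 = 0.08, two-sided alpha 0.05, power 0.80, 336 patients in 8 hospitals per arm.

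- Unclustered size: n = [1.96·√(2·0.14·0.86) + 0.842·√(0.20·0.80 + 0.08·0.92)]² / 0.12², which rounds up to 131 per arm.
- Mean cluster size: 336/8 = 42.
- No single intracluster correlation is stated for local recurrence, so 336 cannot be reproduced from stated inputs alone. It implies a design effect of 336/131 = 2.565, and so a correlation of (2.565 − 1)/(42 − 1) = 0.038. An assumed 0.04 gives 346 per arm.

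The planned figure is therefore plausible, and the design effect of 2.565 is carried forward unchanged.

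**3. Equal loss in both arms.** The share f of recurrences lost is not in the documents; 5% to 20% is an assumption. Observed rates are 0.20(1 − f) and 0.08(1 − f). Power uses 336/2.565 = 131 effective patients per arm.

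| f | Control | Intervention | Difference (points) | Risk ratio | Power |
|---|---|---|---|---|---|
| 0 | 20.0% | 8.0% | 12.0 | 0.40 | 80% |
| 5% | 19.0% | 7.6% | 11.4 | 0.40 | 78% |
| 10% | 18.0% | 7.2% | 10.8 | 0.40 | 75% |
| 20% | 16.0% | 6.4% | 9.6 | 0.40 | 70% |

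The factor (1 − f) cancels in the risk ratio. The odds ratio, which the Analysis section names for binary outcomes, barely moves at f = 10%: (0.08/0.92)/(0.20/0.80) = 0.348 becomes (0.072/0.928)/(0.18/0.82) = 0.353.

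In events, the design expects 336 × 0.20 = 67.2 in control and 336 × 0.08 = 26.9 in intervention. A 10% loss removes 6.7 and 2.7 of these.

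**4. Unequal loss, for direction only.** A loss of 5% in control and 20% in intervention gives 19.0% v 6.4%, ratio 0.34. The reverse gives 16.0% v 7.6%, ratio 0.475. Either direction is arithmetically possible.

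**The case against.** **The gap is narrow.** A reader might infer that every asymptomatic recurrence found on imaging is lost. The definition does not support that: signs and symptoms are alternatives, and hydronephrosis or invasion needs no symptom. Only a mass with neither is left out. This objection stands.

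**Most such patients would qualify later.** The Background describes local recurrence as usually inoperable and often painful, and charts are reviewed every three months for at least 30 months. Many cases would probably meet a tier in time. A reader might infer that late dating then distorts the result. But the outcome is a hospital rate, a case that qualifies within follow-up still counts in it, and the Analysis section does not tie the hazard ratio to local recurrence. This also stands. What remains is the patient who does not qualify before follow-up ends. Biopsy cannot be relied on to close that gap: primary outcomes come from chart review without patient contact, so the study cannot call for one.

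**No difference between arms is shown.** A reader might infer that closer follow-up in intervention hospitals would lower their apparent recurrence rate. The described interventions concern surgical technique and decision-making, not follow-up imaging or biopsy, and data are collected in the same way in both arms. Surgeons know their arm, but nothing in the document says this changes imaging or biopsy. The unequal scenarios in step 4 therefore have no basis in the documents.

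**A full protocol or abstraction manual may deal with it.** It may. But the point is not missing detail: the article states criteria, and those criteria exclude the case. A manual that counted it would depart from the published definition. Nor do the two sections contradict each other, since Cancer Centre charts also hold histology, signs and symptoms.

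**Redefining a primary outcome after accrual is itself a risk.** This is fair, and it limits how the change should be made.

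**Conclusion.** The point holds in a limited form. Read as written, the definition scores as recurrence-free an unbiopsied pelvic mass with no listed sign or symptom, whatever its growth or recorded treatment, unless a qualifying feature appears within follow-up. This is a flaw in a stated rule.

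Its size is unknown. The documents give neither the number of such patients nor any difference between arms. With equal loss the cost is events and some power: about 78%, 75% or 70% at an assumed 5%, 10% or 20%, against about 80% planned, with the risk ratio unchanged. These figures assume the design rates and the design effect implied by 336 per arm. The matter is worth correcting because the remedy is cheap, not because the result has been shown to be biased.

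**What to change.** Before outcome data are compared by arm:

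- Extend *probable* to a pelvic mass at the operative site that enlarges on successive imaging, or that the hospital or Regional Cancer Centre chart documents as diagnosed and treated as local recurrence, with or without symptoms.
- Do not count a new mass on its own; that would admit any postoperative mass.
- Apply the rule to every chart in both arms, including those already abstracted.
- Classify blind to arm where possible. The diagnosed-and-treated route rests on the judgement of clinicians who may know the arm.
- Report the local recurrence result with and without the added cases, so that the effect of the change is visible. The change reaches the primary result only if *probable* cases count towards it, so state which tiers do.

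The cost is some re-abstraction of imaging reports and clinic notes in charts already under review, and a few benign masses counted as recurrence. No new procedure or patient contact is needed.
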